## Abstract

**Background:**

Perimenopausal insomnia is one of the core symptoms of the menopausal transition. Acupuncture is considered to exert a positive effect on restoring the normal sleep–wake cycle. However, there is little intuitive evidence besides evaluation using clinical effectiveness scales. We therefore designed this study, aiming to use more intuitive and reliable detection techniques such as functional magnetic resonance imaging before and after applying acupuncture to provide neuroimaging evidence, as well as to verify the effectiveness with other curative effect indicators.

**Methods/Design:**

This study is a randomized, assessor–statistician-blinded, positive medicine controlled trial involving 40 participants. A total of 40 eligible patients with perimenopausal insomnia will be randomly assigned to two groups in a 1:1 ratio as an intervention group using acupuncture and a control group taking estazolam. Participants in the intervention group will receive six acupuncture treatment sessions per week for 4 consecutive weeks, for a total of 24 sessions during the study. Meanwhile, the medicine control group will be prescribed estazolam 1–2 mg/day to be taken 30 minutes before sleep for 4 weeks. The primary outcome is the Pittsburgh Sleep Quality Index. Secondary outcomes are the micro-movement sensitive mattress-type sleep monitoring system, the Hamilton Depression Scale, and the Hamilton Anxiety Scale. All outcomes will be evaluated before and after treatment. The safety of interventions will be assessed at every visit.

**Discussion:**

The results of this trial, which will be available in 2018, will investigate the impact of acupuncture treating perimenopausal insomnia from assessment of the sleep architecture, hormone level, and emotional-circuit neurological function, and will uncover the effective mechanism of acupuncture regulating the emotional center integrated effect.

**Trial registration:**

Chinese Clinical Trials Register, ChCTR-IPC-16007832. Registered on 26 January 2016.

**Electronic supplementary material:**

The online version of this article (doi:10.1186/s13063-017-2072-7) contains supplementary material, which is available to authorized users.

## Background

Every woman has to undergo the menopausal transition as an inevitable stage of life. During this period, perimenopausal females usually complain of difficulties initiating and/or maintaining sleep with frequent nocturnal and early morning awakenings. Sleep disturbances are often multifactorial in origin and have a significant impact on the health-related life quality. The Study of Women’s Health across the Nation (SWAN) presents that the prevalence of sleep disturbance ascends with increasing age. Recent reviews revealed that the prevalence of insomnia in the perimenopausal women ranges from 39 to 47% [1], while it is approximately 35% in the general population [2].

In addition, with the increasing socioeconomic stress, there are more and more middle-aged women suffering from mood disorders, such as anxiety and depression, which have been noted to be closely related to sleep problems in postmenopausal women [3]. Difficulty in falling sleep has been shown to associate strongly with anxiety, with nonrestorative sleep also correlating strongly with depression, as well as results in anxiety, irritability, and nonrefresh sleep problems which in turn may manifest as depression [4]. Studies by Guidozzi et al. [5] also showed a significant correlation between depression and sleep-related disorders. According to these findings, sleep difficulties and emotional problems interact with and aggravate each other.

Currently, hypnotic medication such as benzodiazepine receptor agonists (estazolam in particular) has been recommended to be the first-choice medicine used routinely for chronic insomnia. Although estazolam is efficacious in the short-term management of insomnia, there is very limited evidence for long-term treatment efficacy [6]. Additionally, various adverse effects related to their use have been reported, including residual daytime sedation, cognitive impairment, and medication dependence [7–10]. Therefore, a large number of patients with insomnia are turning to complementary and alternative medicine such as acupuncture rather than hypnotic medication.

As a chief component of Traditional Chinese Medicine (TCM), acupuncture has been used frequently in the treatment of a wide range of health problems, especially including sleep disturbance and mood disorder, in China and throughout the world [11, 12]. Previous studies certified that acupuncture appears to have an irreplaceable effect in treating insomnia and is able to significantly improve anxiety and depression [13]. Our pilot study also suggested that acupuncture treatment is effective in increasing sleep quality and improving emotional condition [14]. Consequently, it was believed that acupuncture may have great effect on sleep disorders and mood disturbances. Although there are some available studies demonstrating the benefits of acupuncture treating insomnia via evaluation using clinical effectiveness scales, it is still difficult to list more intuitive evidence, such as functional magnetic resonance imaging (fMRI) results.

Considering that acupuncture may have great relevance for modulation of sleep and mood through a potential central neural mechanism, in this trial fMRI—as a more intuitive and reliable detection technique—will be used to investigate the effectiveness and central neural mechanism in acupuncture treatment for perimenopausal insomnia by a comparison with western medicine. Furthermore, we will research the impact of acupuncture treatment for perimenopausal insomnia via changing the sleep architecture and neural function of the emotional neurocircuitry, consequently revealing the integrated effect mechanism of the emotional center function of acupuncture.

## Methods/Design

### Objectives

The study aims to research the influence of acupuncture on perimenopausal insomniacs, such as determining the difference of brain activity and the relevance between the brain and clinical effects, as well as assessing the effect of acupuncture for perimenopausal insomnia.

### Hypothesis

According to the validity of acupuncture on perimenopausal syndrome, insomnia, and emotional disorder, as well as the influence of acupuncture on brain function, we hypothesize that acupuncture will improve the symptoms of perimenopausal insomniacs, and there will be a difference between acupuncture and medicine control based on the fMRI examination.

### Setting

A total of 40 patients diagnosed with perimenopausal insomnia will be divided randomly into two groups (acupuncture intervention group and western medicine control group) through a completely randomized digital table in a ratio of 1:1. This RCT will be conducted in a single center with the assessor and statistician blinded to treatment allocation, and will be carried out in Sichuan Integrative Medicine Hospital, Chengdu, Sichuan, China.

### Patients

#### Recruitment strategies

There will be three prime strategies to recruit participants with perimenopausal insomnia. The first strategy is to recruit participants from the outpatient and inpatient acupuncture and gynecology department of Sichuan Integrative Medicine Hospital. Second, printed recruitment posters will be distributed in public clinics and nearby communities to enroll potential eligible study subjects. Third, we will post advertisements, through the Internet, social software, and so on, to briefly introduce our study, so as to attract possible patients who are willing to participate.

#### Inclusion criteria

Patients meeting all of the following criteria will be enrolled in the study:Patients meeting the diagnostic criteria for primary insomnia in the *Diagnostic and Statistical Manual of Mental Disorders*, fifth edition [15].Patients meeting the diagnostic criteria for perimenopausal syndrome according to the 2011 criteria of the International Menopause Society [16] and the 2001 criteria of the North American Menopausal Society [17].Chief complaint of sleep disorder.Dextromanuality.Female aged between 40 and 55.The Hamilton rating scale for depression (HAMD) score should be 8 points or higher.The Hamilton rating scale for anxiety (HAMA) count should be 6 points or higher.Voluntarily participating in this study with a written informed consent form signed by the participants themselves.

#### Exclusion criteria

Patients meeting any of the following criteria will be excluded from the study:The insomnia is caused by systemic disease (e.g., pain, fever, cough, surgery, etc.) and environmental disturbance.Diagnoses of diabetes mellitus, cardiovascular disease, serious kidney, lung, or liver diseases, hematological disorders, myasthenia graris, or angle-closure glaucoma.With any contraindications of benzodiazepines and acupuncture.Pregnancy or breastfeeding.With metal objects implanted, or any contraindications for fMRI.Patients with any pathological changes in the brain, such as brain tumors, diagnosed on the basis of skull MRI TIW1 and T2W1 routine examination.Patients who have received acupuncture in the past month and are being treated with hypnotic medications.Patients who have taken psychoactive medications or vasoactive medications in the previous 3 months.Alcohol or drug abuse.Any other condition that the investigator judges as likely to make the patient incapable to complete, comply, or unsuitable for the clinical trial.

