### Procedure

All of the potential participants will be initially assessed according to the inclusion and exclusion criteria by the physicians. After completing a screening test, the eligible participants will be asked to sign the written informed consent before randomization. The study subjects will then enter a baseline period for 1 week without any treatment. Subsequently, they will receive the intervention in the light of their group allocation for 4 weeks. All of the patients will be required to provide blood specimens for testing relevant indexes, as well as to be evaluated by study-related scales, MSMSMS, and fMRI scan before and after treatment. Two weeks after the end of treatment, patients in both groups will be followed up to assess the curative effect and safety again (Fig. 1).

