### Primary outcome

#### Pittsburgh Sleep Quality Index

The Pittsburgh Sleep Quality Index (PSQI), a self-rated questionnaire that evaluates sleep quality and disturbance over 1 month [20], is applied as the primary outcome measurement for clinical effectiveness assessment. The constructive validity and reliability of the PSQI to measure changes of sleep quality have been confirmed in previous studies all over the world. It is widely used to measure response to treatment in research studies and clinical trials. The PSQI is comprised of 19 items which consist of the following seven component scores: subjective sleep quality, sleep latency, sleep duration, sleep efficiency, sleep disturbance, use of hypnotic medication, and daytime dysfunction. Each item is weighted equally on a 4-point scale, from 0 to 3, with 0 indicating no dysfunction and 3 indicating the worst dysfunction. The seven component scores are then added to provide a global PSQI score. In general, a lower global score reflects a better sleep quality [21].

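### As written, the prior-treatment exclusion requires recent acupuncture and current hypnotic use together, so no named criterion excludes a patient with recent acupuncture alone

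*Protocol article*

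**What the plan says.** The Exclusion criteria section opens with a rule that any single item is enough: "Patients meeting any of the following criteria will be excluded from the study". Three of its items matter here.

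- Prior treatment: "Patients who have received acupuncture in the past month and are being treated with hypnotic medications".
- Prior drugs, the item directly after it: "Patients who have taken psychoactive medications or vasoactive medications in the previous 3 months".
- A general clause at the end: "Any other condition that the investigator judges as likely to make the patient incapable to complete, comply, or unsuitable for the clinical trial".

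Under Recruitment strategies, the first of three routes is to "recruit participants from the outpatient and inpatient acupuncture and gynecology department" of the trial hospital. The Procedure section gives one treatment-free interval: "The study subjects will then enter a baseline period for 1 week without any treatment". The primary outcome, the PSQI, is described as "a self-rated questionnaire that evaluates sleep quality and disturbance over 1 month". Under the fMRI examination procedure, both groups are scanned once before and once after treatment. The Trial status section says that recruitment is under way.

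**The concern.** The list works by *any one item excludes*, so the conjunction inside the prior-treatment item decides whom it catches. That item joins two different facts about a patient with 'and'. The next item joins its two drug classes with 'or'. A screener who applies the text as it stands would not use the prior-treatment item to exclude a patient who has just had a course of acupuncture and takes no sleeping tablets.

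The quality of the baseline is at stake. In a trial of acupuncture, a baseline measured while the patient is still under, or just past, the test treatment is not an untreated baseline. This applies to the PSQI, which looks back over a month, and to the first fMRI scan, which is the reference for the pre-post imaging comparison.

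**Working it through.** **Step 1: what the item excludes.** Let A be acupuncture within the previous month and H be current hypnotic treatment.

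| Patient | As written (A and H) | As two separate items (A or H) |
|---|---|---|
| A and H | excluded | excluded |
| A only | not excluded | excluded |
| H only | not excluded by this item | excluded |
| neither | not excluded | not excluded |

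**Step 2: does another item close the two gaps?**

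- H only: largely closed. A patient now on a hypnotic has taken it within 3 months. If hypnotics count as psychoactive drugs, the next item excludes her.
- A only: not closed by any named item. The remaining exclusions concern the cause of the insomnia, diseases, contraindications, pregnancy or breastfeeding, metal implants and fMRI contraindications, brain pathology, the drug classes above, and alcohol or drug abuse. Only the general clause could apply. It does not mention earlier acupuncture and sets no interval, so it can be applied differently from patient to patient.

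**Step 3: does the untreated week clear the PSQI window?** Inputs from the document: untreated period 1 week = 7 days; PSQI recall 1 month; treatment 4 weeks = 28 days. Assumption: a month is 30 days.

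- Baseline PSQI at the end of the untreated week: 30 − 7 = 23 days of recall fall before that week, and 23/30 ≈ 77%.
- Baseline PSQI at the start of that week: all 30 days fall before it.
- PSQI at the end of treatment: 30 − 28 = 2 days of recall fall before treatment starts. These lie inside the 7 untreated days, so this recall window does not reach any earlier acupuncture.

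The direct overlap therefore affects the baseline PSQI and not the end-of-treatment one. The 23 to 30 days are the most that could be affected in a patient with recent acupuncture; they do not measure an effect.

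**Step 4: what this does to the comparisons.**

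- Between arms: allocation is random and 1:1, so recently needled patients are expected in equal proportion in both arms, and a baseline shift is expected to be the same in both. With 20 per arm, each such patient is 1/20 = 5% of an arm, so chance imbalance is possible but has no expected direction.
- Within arms: the fMRI data processing section plans paired *t* tests on cortical measures. Balance between arms does not protect a within-arm pre-post comparison from a reference scan taken soon after acupuncture. The document does not allow the direction or size of that effect to be worked out.

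The document gives neither the share of entrants with recent acupuncture nor the size or persistence of its effect on the PSQI. No sample-size, power or alpha figure depends on this point.

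**The case against.** The strongest reply is that nobody meant the joint rule. If current hypnotic users are already caught by the psychoactive-drug item, a joint rule excludes almost no one further. The item does real work only if recent acupuncture excludes by itself. The list also uses 'and' loosely elsewhere: the first item links systemic disease and environmental disturbance, which cannot sensibly both be required. This is persuasive about intent, and it makes the fault a drafting slip and not a design decision. It does not remove the fault, because screeners apply the written text and patients are being recruited under it.

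There are also mitigations. The investigator can use the general clause. The untreated week gives some separation. Every entrant must still meet the insomnia criteria with sleep disorder as the chief complaint. Gynecology, posters and online advertising supply patients as well. All of this stands and limits the likely extent. It does not supply the missing exclusion.

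A reader might infer three stronger things, none of which the document supports.

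- *That control patients carry the test treatment into the comparison and shrink the between-arm difference in proportion to their share.* The same patients are expected in the acupuncture arm. The end-of-treatment recall window misses the earlier acupuncture (step 3). A loss of contrast would also need an effect that lasts through the untreated week and 4 weeks of treatment and acts differently in the two arms.
- *That recently needled patients are certain to be enrolled.* The recruitment route makes it foreseeable, but no share is given.
- *That the contraindication item, "With any contraindications of benzodiazepines and acupuncture", admits patients contraindicated for one treatment only.* Its ordinary meaning, under 'any', is a contraindication to either. It joins two nouns and not two conditions on the patient, so it is not the same fault.

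**Conclusion.** The point holds as a defect in an operative eligibility rule. Read literally, the prior-treatment item excludes only patients who meet both conditions, and recent acupuncture alone is left to general discretion. The consequence is a possible one: the baseline PSQI and the first fMRI scan may partly reflect earlier acupuncture, since one untreated week leaves up to 23 of 30 recall days exposed (all 30 if the PSQI is completed when that week begins). This rests on a 30-day month and on such patients presenting.

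The size of any effect on the PSQI or on imaging cannot be derived from the document. It is expected to be balanced between arms, so neither a dilution percentage nor a systematic bias towards one arm should be claimed. The point should be corrected because the rule is wrong as written and the correction is nearly free, not because harm to the primary comparison has been shown.

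**What to change.** Replace the single item with two separate exclusions, either of which suffices: acupuncture within the previous month, and current treatment with a hypnotic. If the sponsor did intend the two conditions to apply only jointly, the protocol should say so and justify admitting recently needled patients to an acupuncture trial.

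Because recruitment is under way, check the records of patients already enrolled for acupuncture in the month before entry, and report how many there are in each arm.

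Optionally, and only as a wording clarification, use 'or' in the contraindication item, so that it plainly covers a contraindication to either treatment.

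The cost is a short eligibility edit, one record check and slightly fewer eligible patients from the acupuncture clinic. The planned sample size and analyses are unchanged.

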#### Withdrawal or dropout criteria

The participant has an adverse event related to the research.At the participant’s own request.

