### Sample size

There is so far still no definite sample size calculation for fMRI research; however, as a result of previous fMRI studies, there should be at least 10 participants in each group to obtain brain imaging with statistical significance [18]. Combining the preceding clinical trial experiences all over the world recently with the withdrawal rate, we plan to enroll a total of 40 participants with 20 patients in each group.

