#### Outcome assessments/measurement

All of the outcomes will be assessed twice before and after the intervention treatment.

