### Follow-up

The follow-up assessment, which is designed to evaluate the clinical curative effect and long-term effects of acupuncture, as well as safety of the study, will be carried out 2 weeks after the end of treatment. Patients will document the details of clinical symptoms and adverse events, and send the relevant information to researchers via call, email, or short message service.

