### Statistical analysis

In this study, statistical analysis will be performed by a professional statistician blinded to the whole trial process using SPSS19.0 statistical software, and based on the intention-to-treat principal and preprotocol population. All demographic, baseline characteristics, curative effects, and fMRI images of the subjects will be analyzed with different approaches.

In terms of the data description, the enumeration data/quantitative data will be expressed with/as a percentage or proportion, while the measurement data/qualitative data will be represented as average and standard deviation. On this occasion of normal distribution and homoscedasticity, one-way analysis of variance (ANOVA) will be applied to identify differences in measurement data/qualitative data of comparison. Other covariates will be considered for further revision and if necessary stated in the statistical analysis project prior to data lock. Similar analysis of covariance (ANCOVA) models will used for secondary analysis to adjust baseline characteristics. A *q* test (Newman–Keuls) will be used for pairwise comparison. In case of nonnormally distributed data and heteroscedasticity data, a nonparametric test (Kruskal–Wallis *H* test) will be performed, and a rank sum test (Nemenyi) will be conducted to identify difference between groups. The enumeration data/quantitative data will be compared by chi-square test, while classification data will be evaluated with a rank sum test. In addition, the exploratory analysis will be implemented to describe group means over time. A two-sided test will be applied for available data and *p* < 0.05 will be taken as significant for each outcome. Missing data will be explored and if necessary multiple imputations will be utilized.

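### The withdrawal rule covers any research-related adverse event, however minor, and does not separate stopping treatment from leaving the study

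*Protocol article*

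**What the plan says.** All references are to the protocol article.

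- **Withdrawal or dropout criteria.** There are two. The first is "The participant has an adverse event related to the research"; the second is the participant's own request. The heading treats withdrawal and dropout as one category.
- **Outcome assessments/measurement.** "All of the outcomes will be assessed twice before and after the intervention treatment". The paragraph on the Hamilton scales shows that this means once before and once after treatment. The primary outcome, the PSQI, is "a self-rated questionnaire that evaluates sleep quality and disturbance over 1 month".
- **Procedure.** All patients are to be rated on the study scales before and after treatment. Two weeks later, "patients in both groups will be followed up to assess the curative effect and safety again".
- **Follow-up.** At that contact, "Patients will document the details of clinical symptoms and adverse events", reported remotely. No scale is named.
- **Statistical analysis.** The analysis is "based on the intention-to-treat principal and preprotocol population" (the last term is evidently per-protocol). On gaps in the data: "Missing data will be explored and if necessary multiple imputations will be utilized".
- **Sample size.** "we plan to enroll a total of 40 participants with 20 patients in each group". The withdrawal rate is mentioned but given no value.
- **Safety monitoring and Background.** The adverse events foreseen for acupuncture include subcutaneous hematoma. Those listed for hypnotics include daytime sedation.

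**The concern.** The criterion is stated in full, and it is broad. Other sections use finer distinctions: the exclusion criteria rely on investigator judgement, and Safety monitoring gives serious events their own reporting route. The withdrawal rule uses neither. Staff who apply it as printed would withdraw a patient for a bruise or for morning drowsiness once the event is judged related to the research.

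If withdrawal also ends assessment, her post-treatment PSQI is lost. No intermediate PSQI is planned, so imputation has only baseline information and arm to work from. The reason for the loss would be tolerability of the assigned treatment, so the missing values could be informative. The two treatments have different expected side effects and different contact patterns (24 acupuncture sessions, against weekly face-to-face visits plus daily remote medication checks), so the loss could also differ between arms. The trial has little room for this at 20 patients per arm.

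**Working it through.** **1. Does any other section narrow the rule?** Safety monitoring says that events will be properly dealt with, which suggests management and not automatic removal, but the withdrawal criterion is not tied to it. No section gives a severity grade or provides specifically for assessing a withdrawn patient.

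**2. Is the post-treatment PSQI stated to be lost?** No. The word dropout points that way. The Procedure section, which requires the scales of all patients after treatment, and the intention-to-treat principle point the other way. The three statements do not fit together, and the text does not settle which governs.

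**3. The plan's own figure.** The total of 40 rests on an imaging minimum of 10 per group plus an unquantified withdrawal allowance. No PSQI effect size, SD, power or withdrawal rate is given, so there is no planned power to reproduce or to compare against.

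**4. How many patients might qualify?** The document gives no event rates, so these are assumptions.

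- At 5%, 10%, 20% or 30% per arm, 20 × rate gives 1, 2, 4 or 6 patients. The chance of at least one, 1 − (1 − rate)^20, is 64%, 88%, 99% or over 99%.
- For acupuncture alone, an assumed and independent risk per session of 0.5%, 1% or 2% over 24 sessions gives 1 − (1 − x)^24 = 11%, 21% or 38%, or about 2, 4 or 8 of 20.

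**5. Shift in one arm's mean if those patients are not assessed.** Let p be the fraction lost and D the difference in post-treatment PSQI between lost patients and completers. The full-arm mean is (1 − p)·Mc + p·Md, so the completers' mean is off by p·D.

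| Lost | p | D = 2 | D = 3 | D = 5 |
|---|---|---|---|---|
| 2 of 20 | 0.10 | 0.2 | 0.3 | 0.5 |
| 4 of 20 | 0.20 | 0.4 | 0.6 | 1.0 |

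Equal loss with the same D in both arms cancels in the between-arm difference. Unequal loss does not.

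**6. What imputation from arm and baseline PSQI repairs.** If loss depends only on baseline, the remaining shift is about 0. If it depends on the post-treatment state, lost patients differ at baseline by r·D (equal SDs, correlation r). The regression then recovers r·(r·D) = r²·D and leaves p·D·(1 − r²).

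| r | Share left | p = 0.10, D = 3 | p = 0.20, D = 3 |
|---|---|---|---|
| 0.3 | 91% | 0.273 | 0.546 |
| 0.5 | 75% | 0.225 | 0.450 |
| 0.7 | 51% | 0.153 | 0.306 |

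A simulation with 2,000,000 draws, logistic selection on the post-treatment value and an assumed SD of 3.5 gave shares of 0.91, 0.76 and 0.53 at p = 0.10, and 0.92, 0.77 and 0.54 at p = 0.20. These agree closely with the formula.

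**7. Precision.** With the same assumed SD, the standard error of the between-arm difference at 20 per arm is 3.5 × √(2/20) = 1.1 points. A shift of 0.3 is about a quarter of that, and 0.6 about half. The difference detectable with 80% power at two-sided 0.05 is (1.96 + 0.84) × √(2/n) SD: 0.89 SD at 20 per arm, 0.93 at 18 and 0.99 at 16.

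**The case against.** The strongest reply is that this is a condensed article. Grading of events, the split between stopping treatment and leaving the study, and assessment after withdrawal may all be in the full protocol. That would answer a complaint about silence, but the point here is a criterion that is printed and too wide. An analysis plan cannot repair it either, because it cannot supply a PSQI that nobody sought.

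A second reply is that the sensible reading is milder: a bruise is treated and the patient carries on, all patients are rated after treatment, and both groups are followed up. This largely stands as a reading of intent. It does not change the wording that staff would apply.

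A third reply is that the numbers are small and rest entirely on assumptions. This stands too. A shift of 0.3 points is minor beside a standard error of about 1.1, different kinds of side effect need not mean different rates of withdrawal, and the sample size already allows for some loss.

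A reader might infer more: that the protocol ends assessment of anyone with a related event, contradicts intention-to-treat outright, and so biases the primary comparison. The document does not support that. It never says that assessments stop, it requires post-treatment scales of all patients, and it gives no event rate from which a bias could be computed. Nor is the single post-treatment PSQI a fault in itself, since the instrument looks back 1 month and treatment lasts 4 weeks.

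**Conclusion.** The point holds as a badly worded rule with an avoidable risk. Any research-related adverse event meets a withdrawal or dropout criterion, and the text does not say whether the patient then stops treatment, leaves the study, or both. Followed literally, the rule can remove patients for treatment-related reasons before the only named post-treatment PSQI. That fits poorly with intention-to-treat and with the requirement to rate all patients after treatment.

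The size is unknown. The illustration of 0.2 to 1.0 PSQI points in one arm depends on assumed losses of 2 to 4 of 20 and an assumed D of 2 to 5. What survives imputation ranges from about none, if loss depends only on baseline, to about 91%, if it depends on the post-treatment state and r is 0.3. The two-week follow-up may include a PSQI that the text does not name, and the process chart is not available to check. The change is worth making because it costs so little, not because a large bias has been shown.

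**What to change.** Replace the first criterion with wording to this effect:

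> Study treatment is stopped for a research-related adverse event only when the investigator judges that continuing would be unsafe. Stopping treatment does not end participation. The end-of-treatment PSQI, HAMD and HAMA are still sought from every randomised patient unless she withdraws consent or the investigator judges a particular assessment unsafe. She remains in the intention-to-treat analysis and may be left out of the per-protocol set.

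This keeps patient protection, including the investigator's power to omit an unsafe assessment. It needs no new visit, instrument or patient, and the article reports that the trial is still recruiting, so it can take effect. The costs are some effort to call back patients who have stopped treatment, and PSQI scores that may partly reflect other treatment taken afterwards. Recording such treatment would help in interpreting those scores.
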